#### Other outcome measures

##### The severity and impact of UI on quality of life

It will be assessed by the ICIQ-SF questionnaire; this questionnaire was translated into Brazilian Portuguese and culturally validated by Tamanini et al. [24] and consists of six questions with the aim of evaluating UI frequency, its perceived cause, severity, and its impact on quality of life. These will be measured using the total ICIQ-SF score (sum of questions one, two and three); the scores for this instrument range from 0 to 21 points, where higher scores indicate greater severity.

##### Sexual function

Sexual function will be assessed using the Female Sexual Function Index (FSFI) with cross-cultural validation [25], revealing a Cronbach’s *α* of 0.96. This questionnaire consists of 19 questions grouped into six areas: desire, arousal, lubrication, orgasm, satisfaction, and pain. The sexual function score at the end of the analysis can vary from 2 to 36 points, and the higher the score obtained, the better the woman’s sexual function.

Values equal to or below 26.55 in the general score are considered indicative of sexual dysfunction. There is also a cutoff point for each domain as follows: desire ≤ 4.28, arousal ≤ 5.08, lubrication ≤ 5.45, orgasm ≤ 5.05, satisfaction ≤ 5.04, and pain ≤ 5.51 [26].

##### Dyspareunia

The intensity of dyspareunia will be used on a numerical assessment scale from 0 to 10, with 0 representing “no pain” and 10 the “worst pain imaginable” [27].

##### Self-esteem

The Self-Esteem Scale developed by Rosenberg [28] will be used. This scale was validated for the cancer population [29] and in Brazil [30]. It also received a validation review [31] with Cronbach’s *α* of 0.90. It is a unidimensional measure composed of ten statements related to a set of feelings of self-esteem and self-acceptance that determine global self-esteem. The total scale score varies from 10 to 40 points, being used for categorization: (1) satisfactory or high self-esteem, those with a score greater than 31 points; (2) average self-esteem, total score between 21 and 30 points; and (3) unsatisfactory or low self-esteem, with a score below 20 points. It is understood, therefore, that the higher the value achieved by the woman on the scale, the better her self-esteem.

##### Pain

A numerical scale from 0 to 10 will be used to assess pain, with 0 representing “no pain” and 10 the “worst pain imaginable” [27]. Participants will receive a body diagram to identify the topography of the pain.

##### Fecal incontinence

A validated and culturally adapted self-report questionnaire will be used [32], the Fecal Incontinence Quality of Life (FIQL) questionnaire, which is specific to evaluating the impact of FI on quality of life, the results for intra- and inter-examiner reproducibility showed agreement significant in all domains of the questionnaire, Kappa coefficient lifestyle 0.93, behavior 0.93, depression 0.95, and embarrassment 0.92. It contains 29 questions, which allow calculating impact scores on quality of life on four scales: lifestyle, behavior, depression, and embarrassment. The lower the score on each scale, whose score can vary from 1 to 5, the lower the functional status of quality of life.

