**Methods:**

Two-arm randomized clinical trial: an intervention group (IG) will evaluate the effect of a telerehabilitation program on women undergoing clinical practice of radiotherapy for the treatment of gynecological pelvic cancer and a control group (CG) will maintain the routine. Primary outcome is the prevalence of reports of UI, which will be assessed using the International Consultation on Incontinence Questionnaire—Short Form (ICIQ-SF). The secondary outcomes will be the severity and impact of UI on quality of life, location and perception of pain intensity, presence and intensity of dyspareunia, vaginal stenosis, fecal incontinence (FI), and levels of physical activity. Statistical analysis will be performed by intention-to-treat, and multivariate mixed effects analysis will be used to compare results.

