## Background

Advances in treatment for gynecological pelvic cancer have improved women’s survival, but as a side effect, the risk of pelvic floor (PF) dysfunction has increased [1, 2]. A systematic review showed that the main PF dysfunctions after treatment of gynecological neoplasms are urinary incontinence (UI), fecal incontinence (FI), and sexual dysfunctions [3]. Other PF dysfunctions include vaginal stenosis [4], pelvic pain [5], and decreased muscle function [6]. This type of cancer sensitizes a woman’s feminine identity, as it causes sexual dysfunctions [5, 7–9], dyspareunia [6–8], low self-esteem [8, 10], decreased quality of life [7, 8], and decreased physical activity [11, 12].

It is found in the literature through a systematic review that pelvic floor muscle training exercises (PFMT) is the first line of treatment for UI [13], in improving sexual function [14, 15], and in vaginal stenosis [16]. PFMT is defined as an exercise to improve strength, endurance, power, and relaxation or a combination of these factors [17]. It is certified in the literature on telerehabilitation using PFMT in the treatment of PF dysfunctions and promoted a significant improvement in urinary symptoms, PFM function, and quality of life [18].

Telerehabilitation has become increasingly common, the availability and accessibility of care for women who live far from rehabilitation centers becoming increasingly viable [19]. It is important to highlight that telerehabilitation has educational and self-application objectives that require the development of educational support material that is suitable for the virtual environment. Educational videos and applications have great potential to contribute to virtual care, but there are few materials of this type specifically designed for this purpose that have been tested for their usefulness prioritizing a physical activity plan and self-care measures to contribute to a better quality of life for women [20].

Considering that cancer pelvic is currently among the health problems in the world, and its treatment contributes to PFM dysfunctions such as UI, it is urgent to investigate in high-quality RCTs new low-risk interventions capable to optimize the results obtained through telerehabilitation. Thus, this protocol study aims to evaluate the impact of a telerehabilitation and self-care program on PF dysfunctions, reports of UI, and physical–emotional factors of participants post-treatment for gynecological pelvic cancer.

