## Methods

### Study design

Randomized and controlled, two-arm blinded evaluator clinical trial was designed to evaluate the effect of a telerehabilitation program in women undergoing clinical practice of radiotherapy and brachytherapy of gynecological pelvic cancer on the primary outcome of the prevalence of reports of UI, which will be evaluated using the following question from the International Consultation on Incontinence Questionnaire—Short Form (ICIQ-SF) “how often do you lose urine?”.

Secondary outcomes will be the severity and impact of UI on quality of life, sexual function, FI, self-esteem, quality of life, location and perception of pain intensity, presence and intensity of dyspareunia, vaginal stenosis, and physical activity levels. Finally, the intervention group will respond about treatment satisfaction, adherence to supervised sessions, home guidance through home diary recording, recording of adverse effects, and System Usability Scale.

Participants will be randomized to an intervention group that will participate in a telerehabilitation program or control group. This protocol will be reported according to the Protocol Items Standard: Recommendations for Intervention Trials checklist (SPIRIT) 2013: items recommended for a clinical trial protocol and related documents. It is a superiority trial.

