### Eligibility criteria

The study will consist of participants with UI after radiotherapy and/or brachytherapy for gynecological pelvic cancer who underwent treatment at the Oncological Research Center—CEPON in Florianópolis, Santa Catarina, Brazil.

Women are defined as inclusion criteria: age group over 18 years old; clinical stages I to III of gynecological pelvic cancer; having undergone surgery, radiotherapy, and/or brachytherapy; reporting stress UI, urgent UI, or mixed UI (self-reporting by the question Short Form (ICIQ-SF) “how often do you lose urine?”); do not have orthopedic or neurological limitations that prevent the practice of the telerehabilitation program; and not undergoing physiotherapeutic treatment.

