### Statistical analysis

Data will be de-identified, encoded, and stored in the database using the Excel Program. The software SPSS 22.0 will be used for the analysis of data. The description of quantitative variables will be expressed in mean, standard deviation, minimum value, median, and maximum value. Qualitative variables will be described in absolute and relative values (%). For all primary and secondary results, a 95% confidence interval and a significance level of 0.05 will be considered in the test. Both per-protocol and intention-to-treat analysis will be performed.

A linear mixed-effect model will be used to analyze the ICIQ-SF score, FSFI score, FIQL score, EORTC score, IPAQ score, ROSEMBERG score, and System Usability Scale. In the reassessment, individuals’ values will be considered random effects, and the groups, the times, and the interaction between them will be regarded as fixed effects. In addition, the McNemar test will verify changes in categories variables before and after the intervention. Both per-protocol analysis [21–23] and an intention-to-treat analysis will be also conducted. The Cohen effect size (*d*) will be calculated using the averages.

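### Fecal incontinence (FI) is a named secondary outcome, but its only assigned instrument measures FI-related quality of life, so the trial as described cannot show whether FI occurs less often

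*Protocol article*

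**What the plan says.** The Background counts FI among the main pelvic floor (PF) dysfunctions after treatment: "the main PF dysfunctions after treatment of gynecological neoplasms are urinary incontinence (UI), fecal incontinence (FI), and sexual dysfunctions". It gives the trial's aim as to "evaluate the impact of a telerehabilitation and self-care program on PF dysfunctions, reports of UI, and physical–emotional factors of participants". The Abstract's list of secondary outcomes includes "vaginal stenosis, fecal incontinence (FI), and levels of physical activity". Study design has FI as its own entry, apart from quality of life: "Secondary outcomes will be the severity and impact of UI on quality of life, sexual function, FI, self-esteem, quality of life".

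The section on fecal incontinence assigns the FIQL, "which is specific to evaluating the impact of FI on quality of life". It describes 29 questions giving four impact scores (lifestyle, behavior, depression, embarrassment), each from 1 to 5 with lower meaning worse. Table 2 lists no other instrument for FI. Stool consistency has its own row, with the Bristol scale.

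On symptoms, Eligibility criteria requires only "reporting stress UI, urgent UI, or mixed UI" and does not mention FI. Statistical analysis says: "A linear mixed-effect model will be used to analyze the ICIQ-SF score, FSFI score, FIQL score". It names no endpoint for FI occurrence.

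**The concern.** The outcome is FI, but the measure is what FI does to daily life. These can move apart. A woman may leak as often as before and be less troubled by it after 12 weeks of education and group support. She may also leak less and still be embarrassed. An FIQL difference between arms would therefore not establish less FI, and no difference would not establish that FI was unchanged.

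Entry by UI adds to the problem. The protocol gives no FI prevalence and describes no item that identifies the women who have FI at baseline. A reader could not tell how many women an FIQL result rests on.

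The risk is in the report: following the plan, an FIQL result would appear under the name FI. An analysis plan written later could not repair this, because occurrence data not collected at baseline and 12 weeks cannot be recovered.

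**Working it through.** The protocol states no figure on this point, so there is none to reproduce. The main check sets its sections side by side.

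**1. What could record FI occurrence?**

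| Source | What it is described as recording |
|---|---|
| FIQL (Fecal incontinence; Table 2) | Impact of FI on quality of life, four scales |
| Bristol scale | Stool consistency |
| EORTC QLQ-C30 (Quality of life) | Bowel items named are constipation and diarrhea, not leakage |
| Data collection | Says the questionnaire covers FI, but adds no instrument |
| Statistical analysis | FIQL score in a mixed model; McNemar test for categorical variables, with no FI category defined |

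No described item records the presence or frequency of FI.

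**2. Does the protocol separate occurrence from impact elsewhere?** Yes. For UI, Primary outcome measures uses a 0 to 5 frequency item that starts at never, and the ICIQ-SF total serves separately for severity and impact. For dyspareunia, Study design names both presence and intensity. FI has impact only.

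**3. How many women would have FI?** The protocol gives no prevalence, so 20% to 40% is an assumption.

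- 58 × 0.20 = 11.6 women
- 58 × 0.40 = 23.2 women

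**4. How would an FIQL effect look across all women?** Assume a 0.5-point difference among women with FI, and women without FI near 5 at both visits.

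- 0.5 × 0.20 = 0.10 points
- 0.5 × 0.40 = 0.20 points

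All three inputs (FI share, effect, near-ceiling scores) are assumptions, so these figures are illustrative only.

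**5. What could a yes/no FI outcome show with 29 per arm?** Power for a halving, two-sided α = 0.05, normal approximation:

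Φ[(d − 1.96 × se0) / se1], with d = p1 − p2, se0 = √[2 p̄(1 − p̄)/29], se1 = √{[p1(1 − p1) + p2(1 − p2)]/29}.

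At p1 = 0.20 and p2 = 0.10: p̄ = 0.15, se0 = √(2 × 0.1275/29) = 0.0938, se1 = √(0.25/29) = 0.0928. Then (0.10 − 1.96 × 0.0938)/0.0928 = −0.90, so power is 18%.

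| Assumed FI share | Women with FI (of 58) | Power, 29 per arm | Per arm for 80% power |
|---|---|---|---|
| 10% | 5.8 | 11% | 435 |
| 20% | 11.6 | 18% | 199 |
| 30% | 17.4 | 27% | 121 |
| 40% | 23.2 | 38% | 82 |
| 50% | 29.0 | 50% | 58 |

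**6. Would restricting the FIQL analysis to women with FI recover much power?** Simulated t-test on change, 29 per arm, 0.5-point effect, near-constant scores in women without FI. The SD of change among women with FI is assumed.

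| Assumed SD of change | FI share | Power, all women | Power, women with FI only |
|---|---|---|---|
| 0.8 | 20% | 14% | 15% |
| 0.8 | 30% | 21% | 22% |
| 0.8 | 40% | 29% | 30% |
| 0.5 | 20% | 26% | 32% |
| 0.5 | 30% | 42% | 49% |
| 0.5 | 40% | 56% | 62% |

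Restriction gains 1 to 7 percentage points. Women without FI shrink the mean difference, but they also add almost no variance. The shortage is of women with FI.

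**The case against.** The strongest reply is that the protocol never promises FI prevalence. It uses that word for UI only, and the section on fecal incontinence says openly that its instrument scores impact on quality of life. On this view the label is loose and the measure is not wrong. Most of this stands: presence and frequency are not the stated FI outcome, and a reader who infers that they were promised goes beyond the text. What remains is that FI is listed separately from quality of life and counted among the dysfunctions that the program is meant to affect. A report that follows the outcome list would present impact scores as an effect on FI.

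Four further limits stand.

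- This is a journal article and the interview form is not shown. The supportable statement is that no occurrence item is described, not that none is asked.
- The documents do not say how women without FI score on the FIQL. Ceiling scores, and the dilution that follows from them, cannot be asserted as fact.
- Which women enter the FIQL analysis is commonly left to a statistical analysis plan, so the lack of a stated restriction is not a fault here. Restriction to women with FI at baseline would also drop FI that begins during follow-up, and it gains little power.
- An added FI question would itself have low power with 29 per arm. It would still give a direct estimate of occurrence and show how many women have FI.

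**Conclusion.** The point holds as a mismatch between a named outcome and its measure. As described, the trial can report FI-related quality of life but cannot show whether FI occurs less often, and an FIQL result in either direction should not be read as an effect on FI itself. This rests on the protocol's own description of its instruments and on no assumed number.

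A reader might infer more: that the FIQL analysis is bound to miss a real effect because women without FI sit at its ceiling. The documents do not support that. The 0.10 to 0.20 point figures rest on an assumed FI share, an assumed 0.5-point effect and assumed near-ceiling scores, and the simulation indicates that including women without FI costs little power.

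FI is one of many secondary outcomes. The sample size and the primary UI conclusion are unaffected.

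**What to change.** - Add one question on FI presence and frequency, including a 'never' category, to the baseline and 12-week interviews in both arms.
- Report it by arm as the FI outcome, with a confidence interval for the difference, and state that power is low at 29 per arm.
- Label the four FIQL scales 'FI-related quality of life'. Add a supplementary summary in women who report FI at baseline; do not make it the main FIQL analysis.
- If no question is added, rename the outcome 'FI-related quality of life' in the Abstract, Study design and Table 2, and make no claim about FI occurrence.

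The cost is one extra question in an interview already planned at 60 minutes, plus wording. The relabelling alternative costs wording only. For women already interviewed at baseline without the question, their baseline FI status could not be recovered, so the addition is worth most if made early.

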##### Bristol stool consistency scale

To assess the consistency of feces, adapted for Brazil [33], this Bristol scale has been recognized by scientific literature as a valuable tool in the assessment of intestinal diseases. The general Kappa index was 0.826; the scale demonstrates high reliability in all groups studied.

##### Vaginal stenosis

It will be by self-report using the common terminology criteria for adverse events v.4.0 9 (CTCAE) [34] stenosis classification. On this scale, stenosis is classified into three grades: grade 1 is characterized as asymptomatic shortening or narrowing, grade 2 is shortening or narrowing that does not interfere with physical examination, and grade 3 is shortening or narrowing that interferes with the use of tampons, relationship sexual examination, and physical examination [31].

##### Quality of life

European Organization for Research and Treatment of Cancer Quality of Life Questionnaire C30 (EORTC QLQ-C30). This instrument was created by the European Organization for Research and Treatment of Cancer (EORTC) in 1986, and this is the third version [35]. Validated for the cancer population by Michels et al., [36] Cronbach’s *α* values were 0.72 for global health, 0.86 for the functional scale, and 0.81 for the symptomatic scale.

The instrument consists of 30 questions, being multidimensional and self-administered. Its objective is to evaluate the quality of life in cancer patients in the last 4 weeks. It features five functional scales (physical, functional, emotional, social, and cognitive), a global health status scale, three symptom scales (fatigue, pain, and nausea/vomiting), and six additional symptom items (dyspnea, appetite, constipation, diarrhea, and financial difficulties). The answers are presented in the form of a Likert scale following the classification 1 = not at all, 2 = a little, 3 = a lot, and 4 = a lot. The only exception applies to the global health scale. This consists of two questions that ask the patient to evaluate their health and quality of life in the last week according to scores from 1 to 7.

##### Level of physical activity

The level of physical activity will be investigated using the International Physical Activity Questionnaire (IPAQ—short version) [37]. Brazilian validation and reproducibility were carried out by Matsudo [38] and had a significant Spearman correlation and high reproducibility (rho = 0.69–0.71; *P* < 0.01) and validity of 0.75. It consists of six items that seek to verify the number of times that the subject practiced at least ten continuous minutes of walking, moderate and vigorous physical activity, in the last week, in different involvements, namely work, domestic, leisure, recreational, and sports. After completing the questionnaire, participants can be classified into the categories of sedentary, insufficiently active, and very active. The IPAQ also addresses individuals’ sitting time during the week and on weekends. There are two specific questions that ask: (1) How much time in total do you spend sitting on a weekday? and (2) How much time in total do you spend sitting on a weekend day? Data is presented in minutes per week.

##### Treatment satisfaction

Using a numerical scale, it will be composed of a unidimensional measure to assess treatment satisfaction. Composed of a line from 0 to 10 with anchors at both ends, at one end of the line is marked 10 “completely satisfied” and at the other 0 “dissatisfied”.

##### Home guidelines

A home diary will be delivered to record the PFMT; in this record, the participant will record the number of contractions performed, how many times a week the PFMT was performed, and the position used (infographic 2).

##### Adherence to supervised sessions and recording of adverse effects

A record will be made by the main researcher during the intervention regarding adherence to supervised sessions, as well as adverse effects during the intervention through a diary record.

##### System Usability Scale (SUS)

Post-intervention, participants will investigate the usability of the system used; the System Usability Scale (SUS) instrument contains ten questions that are grouped on a Likert scale, with values from 1 to 5, classified respectively as: “strongly disagree,” “disagree,” “neither agree nor disagree,” “agree,” and “strongly agree”. Only the last question, included by the researcher, was a non-mandatory essay. The estimated total time to answer the questionnaire was 5 to 10 min. After completing the SUS, the total score was calculated, which generated a unique number. To calculate the score, the score of each contributing item is first added together on a scale of 1 to 5. For items 1, 3, 5, 7, and 9, the individual score is the grade received minus 1. For items 2, 4, 6, 8, and 10, the contribution is 5 minus the grade received. The sum of all scores is multiplied by 2.5 and the total SUS value is obtained. After scoring and calculating the score, it is possible to classify the evaluated system: 20.5 (worst imaginable); 21 to 38.5 (poor); 39 to 52.5 (median); 53 to 73.5 (good); 74 to 85.5 (excellent); and 86 to 100 (best imaginable) [39, 40].

##### Descriptive and control variables

The descriptive and control variables were divided into clinical variables (cancer stage, treatment characteristics, previous clinical treatment chemotherapy, teletherapy and brachytherapy, characteristics of the surgical intervention, date of surgery, gynecological–urological history, other diseases, smoker, and use of alcohol), sociodemographic variables (age, education, marital status, economic level, and occupation), and anthropometric measurements (height and body mass). Descriptive and control variables will be acquired by self-report. The study variables referring to the intervention protocol are presented in Table 2.

**Table 2 Tab2:** Outcome measures and time points the study assessment

Results	Instruments	Baseline	Post-intervention
Urinary incontinence and quality of life	International Consultation on Incontinence Questionnaire—Short Form (ICIQ-SF)	√	√
Function sexual	Female Sexual Function Index (FSFI)	√	√
Self-esteem	Self-esteem scale Rosenberg	√	√
Pain	Numerical pain scale	√	√
Body diagram	Topography of pain	√	√
Dyspareunia	Numerical pain scale	√	√
Fecal incontinence	Fecal Incontinence Quality of Life (FIQL)	√	√
Stool consistency	Bristol stool consistency scale	√	√
Quality of life	European Organization for Research and Treatment of Cancer Quality of Life Questionnaire C30 (EORTC QLQ-C30)	√	√
Vagina stenosis	Common terminology criteria for adverse events v.4.0 9 (CTCAE)	√	√
Physical activity level	International Physical activity questionnaire (IPAQ—short version)	√	√
Treatment satisfaction	Numerical pain scale		√
System Usability Scale	(SUS)		√

